#### Demographics

This questionnaire will include a subset of 14 questions about the women’s date and country of birth; state/city of residence; educational level; number of previous pregnancies; number of biological children (including stillbirths); number of people living at home (adults and children); marital status; cohabitation with partner; characteristics of the home (inside and outside spaces in square meters); and living environment changes since the beginning of the pandemic.

#### Coronavirus perinatal experiences (COPE) questionnaires

In order to assess the experiences of the women during the COVID-19 pandemic, a modified version of the Coronavirus Perinatal Experiences - Impact Survey (COPE-IS) [31] will be administered at the baseline assessment. The questionnaire assesses several areas of impact: perinatal experiences related to the COVID-19 pandemic; exposure and symptoms; financial impact; social support impact; social distancing and activity restrictions; coping and adjustment; emotional impact; physical and mental health history and substance use.

In the follow-up assessments, the women’s experiences will be measured using a modified version of the Coronavirus Perinatal Experiences Scale - Impact Update (COPE-IU) [32] and the Coronavirus Perinatal Experiences Scale - Care Follow Up (COPE-CF) [33]. The COPE-IU evaluates exposure to COVID-19, symptoms, impact on daily life, experiences and feelings, whereas the COPE-CF evaluates perceived support and care and the social and financial impact of the pandemic.

The sections included in the modified version of the COPE-IS [31], COPE-IU [32]and COPE-CF [33]are described below.

##### Perinatal health care experiences related to COVID-19

Twenty-six items regarding parity, health problems during pregnancy, type of pregnancy, prenatal and postpartum care support and resources available during this period, changes experienced as a result of the COVID-19 outbreak, and possible concerns about changes in family/friend support, medical care during childbirth and the child’s health. For postpartum women specifically, the survey also includes questions about the infant’s place of birth, breastfeeding, changes experienced in birth plans and level of distress experienced related to changes in birth and postpartum plans [31].

##### COVID-19 exposures and symptoms

Six items about (1) the diagnosis of COVID-19; (2) any symptoms compatible with the coronavirus disease; (3) contact with someone who has been diagnosed with COVID-19; (4) any death of family or friends due to COVID-19; (5) the level of distress about COVID-19-related symptoms or potential illness: (5a) their own illness or (5b) in their friends and family [31, 32].

##### COVID-19 financial impact

Two items about (1) the current employment situation and (2) the financial impact of the COVID-19 outbreak [31, 33].

##### COVID-19 social support impact

Six items about (1) seeking support, (2) support provided, (3) need for support, (4) perceived support; (5) level of distress experienced with disruptions to social support due to the COVID-19 pandemic; and (6) number of weeks participants have been observing the lockdown guidance [31, 33].

##### COVID-19 coping strategies

A total of 23 items regarding potential coping strategies (problem-focused or emotion-focused) to cope with the stress related to the COVID-19 pandemic (for example, “getting a good night’s sleep”; “talking with friends”). The participants must indicate all the strategies that they are implementing [31, 32].

##### COVID-19 emotional impact

Four items assessing the subjective impact of the COVID-19 pandemic. The questions include: (1) overall level of impact on daily life due to the COVID-19 pandemic; (2) overall level of stress related to the COVID-19 outbreak; (3) perceived positive or negative impact of the COVID-19 pandemic; and (4) how long participants think it will take for things to go “back to normal”? [31, 32].

##### Physical and mental health history and substance use

Thirteen items addressing: 1) the women’s and family (partner, child or other members of the household) history of the following medical conditions: respiratory problems, diabetes, heart disease or hypertension, lung disease; liver disease; cancer; disease compromising the immune system; mood and/or anxiety disorders; 2) whether currently receiving treatment for mental disorders (for example, depression, anxiety, stress, ADHD, bipolar disorder, eating disorder or PTSD); 3) current substance use; and 4) current treatment of medical conditions [31].

#### Brief symptom Inventory-18

The Brief Symptom Inventory-18 (BSI-18), omitting suicidality, will be used to evaluate psychological distress [34] in the last week. The BSI-18 is an 18-item self-report questionnaire which includes a summary scale of overall distress, the Global Severity Index (GSI), and three subscales: depression, anxiety, and somatization. Each item is rated on a 5-point scale, with distress ratings ranging from 0 (not at all) to 4 (extremely). For the purposes of the current study, only the GSI will be examined. The GSI level is the summed score of all the items [34].

#### Dependent/outcome measures

##### Edinburgh postnatal depression scale

The Edinburgh Postnatal Depression Scale (EPDS) [35] is the most widely used self-report scale designed to identify women at risk for perinatal depression [36]. The 10-item scale indicates how women felt during the previous week. The items assess symptoms of sadness, anxiety and thoughts about death. Scores range from 0 to 30. The depression level is the sum score of all the items, and higher scores indicate greater symptom severity. A threshold of 13 or more will be used to identify clinically significant symptoms [37]. Although a number of cut-off points have been used in different populations [38], maximum accuracy with a probable diagnosis of depressive disorder has been shown at this cut-off point in reviews of international EPDS validation studies [36–39].

#### Generalized anxiety disorder screener

Symptoms of anxiety will be evaluated using the validated self-report questionnaire Generalized Anxiety Disorder Screener (GAD-7) [40], which is based on criteria from the Diagnostic and Statistical Manual of Mental Disorders (DSM)-IV and DSM-IV-TR [41]. Even though GAD-7 was developed for generalized anxiety disorder, it is also used as a measure for anxiety for research purposes [42, 43] and clinical management for antenatal and postpartum mental health [44]. The seven items assess worry, tension, restlessness, and irritability. The GAD-7 total score ranges from 0 to 21. The anxiety level is the sum score of all the items, with higher scores reflecting greater anxiety severity. We will use a threshold of 10 or more points for a participant to be considered as belonging to a clinical range [14, 40]. The GAD-7 has shown good reliability and construct validity in pregnancy and the postpartum period [40, 45, 46].

#### Post-traumatic stress disorder (PTSD) checklist

Post-traumatic stress symptoms associated with COVID-19 will be evaluated via a subset of 10 questions from the Post-Traumatic Stress Disorder (PTSD) checklist for DSM-5 [47, 48]. These 10 questions ask participants to indicate the extent to which they experienced: (1) Feeling super alert or watchful or on guard; (2) Feeling jumpy or easily startled; (3) Having difficulty concentrating; (4) Trouble experiencing positive feelings; (5) Feeling guilty or blaming yourself; (6) Feeling irritable, angry or aggressive; (7) Repeated disturbing and unwanted thoughts about the COVID-19 outbreak; (8) Repeated disturbing dreams about the COVID-19 outbreak; (9) Trying to avoid information or reminders about the COVID-19 outbreak; and (10) Taking too many risks or doing things that could cause you harm. All items refer to the previous seven days and are answered on a five-point Likert scale, ranging from 0 (Not at all) to 4 (Extremely) with possible total scores ranging from 0 to 40. Higher scores indicate greater symptom severity. The PTSD symptom level is a summed score of all the items [47]. The subset of questions from the PTSD checklist are included in the COPE-IS and COPE-IU questionnaires [31, 32].

### Validation of the questionnaires

We will use available validated versions of the EPDS, GAD-7 and PTSD DSM-5 checklist in the official language of all the participating countries. However, COPE-IS, COPE-IU and COPE-CF are newly developed measures, and psychometric properties are yet to be established. Scoring procedures also need to be determined. The COPE questionnaires were originally available in English and translated to Spanish and German. Thus, researchers from each country involved in the study performed the translation and cultural adaptation of the questionnaires from English into the official language of their country, following several methodological steps, defined a priori, as detailed in Table 2. No major discrepancy was identified in any of the cross-cultural adaptations.

**Table 2 Tab2:** Cross cultural adaptation of the COPE questionnaires

• Adaptation of “demographic variables”	
• Forward and backward translation from the original version	
• A pilot study with a small (*N* ≥ 4) sample of pregnant women and new mothers (to assure comprehensibility of the items as intended)	
• Revision of the instrument by an expert committee (in the perinatal field) in each country (*N* ≥ 2 persons)	

### Ethical standards

This study is conducted according to the principles expressed in the Declaration of Helsinki. Ethical approval was obtained from all the countries before starting the project. Handling of the study data will comply with all the national required standards for data protection. Electronic informed consent will be obtained from all the participants, and the confidentiality of all the information provided will be ensured.

Some survey questions can elicit changes in the emotional state of participants. In order to address this issue, a debriefing procedure will be made available; at the end of the survey, a list of up-to-date services and resources will be provided for each country covering a range of needs, from information about the COVID-19 pandemic to the general mental health and perinatal care services available in each country. Additionally, contact information for the lead research team for each country will be given in case participants would like to request additional information. The researchers will publish the results of the study on the website and will send information about the global results of the study to the participants upon request.

### Data collection

Participants will be recruited through social media advertising (Twitter, Facebook, Instagram, LinkedIn, ResearchGate, WhatsApp, etc.), networks of organizations (including universities, health centers, NGOs working in the field of perinatal mental health), policymakers, local organizations, and other stakeholders (using the network provided by the Riseup-PPD), as well as personal networks of colleagues and acquaintances of the research team members, and direct contact by mobile message or email.

Participants will be asked to click on the project website link (see the general project website: https://momsduringcovid.org) to be directed to the online questionnaire for their specific country. First, they will read an electronic consent form presenting an overview of the study aims, content of the questions asked, potential risks and benefits, and ethical aspects of the study (i.e., voluntary participation, confidentiality and secure storage of the data, and absence of any type of compensation). At the bottom of the form, they will be asked to confirm a set of eligibility criteria and to provide their consent to access the study. Participants who do not meet the predefined inclusion criteria will be directed to a message thanking them for their interest and informing them of the required eligibility criteria for participation in the study.

The baseline questionnaire is estimated to take approximately 20 min to complete. Eligible participants who complete the baseline questionnaire will be invited to provide their email or phone number to be contacted to participate in the three follow-up assessments. Participation in the follow-ups will be optional and participants will need to provide their consent to be contacted by email or phone (text messages only). Attached to this request, we will provide a clear plan to guarantee confidentiality and protection of the contact information provided (this information will also be provided in the Informed Consent).

### Data analysis

Patterns of missingness in the data will be studied and the Expectation-Maximization algorithm will be implemented to impute missing data. Attrition analyses will be carried out to examine differences between participants who completed all the assessments and those who did not. Descriptive statistics will be examined for the study variables for all the assessment times. Measurement equivalence will be studied in order to ensure we are measuring the same variables across countries.

Changes in mental health between baseline and the follow-ups will be examined by testing latent growth curve models for each outcome. Moreover, the relationships between the rates of change in predictors (i.e., risk and protective factors) and mental health results during the follow-up will be analyzed. Multilevel analyses will be performed to control the moderation of demographic variables in those interrelations. Regarding the overall fit of these models, Satorra-Bentler χ^2^, CFI, RMSEA and the confidence interval for the RMSEA statistics will be calculated. Lagrange multipliers and the Wald test will be performed sequentially to improve the fitness of the models, following the hypotheses of the study. Standardized coefficients and measurement equations with scores in R^2^ will be reported. These analyses will be undertaken using the statistical program EQS. 6.3.

To determine the risk and protective factors to predict perinatal mental health outcomes during the COVID-19 pandemic, a random sample of 70% of the data will be used to derive the machine learning algorithms including regularized logistic regression, random forest, decision tree, and gradient boosting to predict the risk of PPD, and their performance, and the remaining 30% for validation. First, in the derivation sample, all the predictors described above will be entered into the models to estimate the probability of depression or anxiety or PTSD. Beginning with a model containing all potential covariates, the variable with the least significant *P* value will be removed and tested using the likelihood-ratio test until all variables left in the model significantly (at alpha = 0.05) contribute to the model.

In regularized logistic regression models, results will be presented as odds ratio (OR) with 95% confidence intervals (CIs). The R^2^ will be used to calculate the proportion of the explained variance of clinical outcomes by the selected predictors. The different aspects of model performance will be studied, including calibration and discrimination. Calibration will be assessed using the Brier score and by plotting the non-parametric estimate of the association between the observed frequencies and the predicted probabilities. The receiver operating characteristic (ROC) curves (and the corresponding area under the ROC curve—AUC) will be calculated to test for discrimination. To correct optimism, internal validation will be performed for each model using the bootstrap procedure with 500 bootstrapped samples. The final models will be selected to derive scores for clinical use, and nomograms will be created. Criteria for this selection will include both discriminant ability (defined by the AUC) and model simplicity. Finally, the coefficients (scores) derived from the derivation cohort will also be validated in the validation cohort. These statistical analyses will be carried out in R and Python. The analyses will conform to the reporting standards of transparent reporting of a multivariable prediction model for individual prognosis or diagnosis (TRIPOD) [49].

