## Methods

### Aim

The main aim of this prospective study is to investigate the impact of the COVID-19 pandemic on perinatal mental health (depression, anxiety, and post-traumatic stress symptoms).

The primary objectives are the following:
To evaluate changes in perinatal mental health outcomes (symptoms and indices of clinical risk for mental disorders) during the COVID-19 pandemic.

We will evaluate the changes in (a) perinatal mental health symptoms (depression, anxiety and post-traumatic stress disorder [PTSD]); and (b) clinical risk indices (proportion of women above the clinical cut-off point on a validated self-report scale) for depression and anxiety disorders. We will compare the results to similar pre-pandemic studies in all the countries. We will also assess the acute and long-term mental health impact of different phases of the COVID-19 pandemic by measuring the changes in perinatal mental health outcomes between the initial survey and the follow-up assessments.
2)To determine the risk and protective factors that predict perinatal mental health outcomes during the COVID-19 pandemic.

We will determine the risk and protective factors that predict PTSD symptoms and the clinical risk of depression and anxiety disorders (proportion of new cases above the cut-off point on validated self-report scales in the follow-up period) during the COVID-19 pandemic. Factors included in our study were based on recent literature [24–28] and include demographic variables, COVID-19 epidemiology and public health measures, perinatal experiences during the COVID-19 pandemic, and psychological distress.

Furthermore, additional secondary objectives related to the impact of COVID-19 on perinatal mental health will also be examined: the comparison of perinatal mental health outcomes between the countries participating in the study; breastfeeding and its protective role in perinatal mental disorders; the risk of perinatal mental disorders in COVID-19-positive women vs. COVID-19-non-positive women; and factors associated with the level of distress of women during the perinatal period.

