### Study design

This is an international prospective observational cohort study, with a baseline and three follow-up assessments: at one, three, and six months post-baseline. The observation period will be 6 months, from the initial evaluation to the last follow-up assessment. The overall study will span from 15 June 2020 to 15 June 2021.

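### Missing data are to be filled by EM imputation with no step for imputation uncertainty although follow-up is optional, so standard errors for follow-up results come out too small

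*Protocol article*

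**What the plan says.** The Data analysis section of the protocol article names the missing-data method: "the Expectation-Maximization algorithm will be implemented to impute missing data". The sentence stands ahead of both the growth models and the prediction models. It sets no limit by type of variable, by outcome or predictor, or by skipped item or missed wave. No repeated draws, pooling or variance correction follow. The next step is descriptive: "Attrition analyses will be carried out to examine differences between participants who completed all the assessments and those who did not". No later analysis is said to use its result.

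The design (Study design) has "three follow-up assessments: at one, three, and six months post-baseline". Under Data collection, "Participation in the follow-ups will be optional and participants will need to provide their consent to be contacted by email or phone". A woman can therefore complete baseline and contribute no follow-up wave.

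Under Aim, the primary objectives include change between the initial survey and the follow-ups, "clinical risk indices (proportion of women above the clinical cut-off point on a validated self-report scale) for depression and anxiety disorders", and prediction of clinical risk defined as the "proportion of new cases above the cut-off point on validated self-report scales in the follow-up period". For the EPDS, "A threshold of 13 or more will be used to identify clinically significant symptoms"; the GAD-7 cut-off is 10 or more.

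**The concern.** EM imputation without repeated draws gives one completed data set. Software that receives it treats a filled-in EPDS or GAD-7 score as a measured one: it counts too many women, and with conditional means it also sees too little spread. Confidence intervals for change, and for the association of risk factors with follow-up outcomes, then come out too narrow.

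A second effect depends on the kind of value filled in. EM in its plain form supplies the conditional mean, which lies nearer the centre than real scores do. When fewer than half of women are truly above a cut-off, this moves women from above it to below it. The follow-up clinical-risk proportion falls, and some true cases are labelled non-cases in the prediction models.

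At stake are the follow-up parts of both primary objectives, and the odds ratios, calibration and clinical scores derived from them.

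**Working it through.** **Inputs.** From the article: optional follow-up, EM imputation, cut-off outcomes, and a minimum of 300 women per country (used here only as n). Assumed, because the article gives no figures: missing share m of 20, 40 or 60% at one follow-up; baseline-to-follow-up correlation r of 0.5 to 0.7; a true 25% above the cut-off; dropout depending only on baseline score (MAR). The plan states no figure on this point to reproduce.

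**Step 1, standard error of mean change, by hand.** Take standardised scores with no true change and, for this step only, missingness unrelated to baseline. Let A = (1−r)² and B = 1−r².

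- Conditional means: the software's variance is [A+(1−m)B]/n; the true variance is [A+B/(1−m)]/n.
- One random residual added: the software's variance is [A+B]/n; the true variance is [A+B/(1−m)+mB]/n.

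At m = 0.2:

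- r = 0.5 (A = 0.25, B = 0.75). Conditional means: √(0.85/1.1875) = 0.846, so a nominal 95% interval covers 2Φ(1.96×0.846)−1 = 90.3%. Random residual: √(1.00/1.3375) = 0.865, coverage 91.0%.
- r = 0.7 (A = 0.09, B = 0.51). Conditional means: √(0.498/0.7275) = 0.827, coverage 89.5%. Random residual: √(0.600/0.8295) = 0.850, coverage 90.4%.

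**Step 2, proportion above the cut-off, by hand.** With conditional means, the share of imputed scores above the cut-off is 1−Φ(z/r), where z = 0.6745 for a true 25%. This is 8.9% at r = 0.5 and 16.8% at r = 0.7. The overall share is (1−m)×25% plus m times that figure:

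- m = 0.2: 0.8×25+0.2×8.9 = 21.8%, and 0.8×25+0.2×16.8 = 23.4%.
- m = 0.4: 0.6×25+0.4×8.9 = 18.6%, and 0.6×25+0.4×16.8 = 21.7%.

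**Step 3, simulation with dropout depending on baseline** (n = 300; 4,000 replicates; ranges span r = 0.5 and 0.7). The missing share is set at an average baseline score; the overall shares are about 21, 41 and 59%. The SE ratio is the software's standard error divided by the true one.

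| Missing | Values filled in | SE ratio, mean change | 95% coverage, mean change | True 25% reads as |
|---|---|---|---|---|
| 20% | conditional mean | 0.82–0.83 | 89–90% | 21.9–23.6% |
| 40% | conditional mean | 0.63–0.67 | 78–81% | 18.5–22.0% |
| 60% | conditional mean | 0.45–0.49 | 61–65% | 15.6–20.3% |
| 20% | with random residual | 0.84–0.85 | 90% | 25.0–25.1% |
| 40% | with random residual | 0.72–0.73 | 84% | 25.0–25.1% |
| 60% | with random residual | 0.60 | 76–77% | 24.9–25.1% |

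**Step 4, a second simulation** (n = 1,000; more than one follow-up wave; correlations 0.55 to 0.65; 500 replicates). Type I error at a nominal 5%, for a null risk factor or a null mean change, was 10–14% with 80% retained at the earlier and 70% at the last follow-up, 17–27% at 60%/50%, and 23–38% at 50%/35%. The lower figures are with a random residual, the upper with conditional means.

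**Step 5, the alternative under the assumptions of step 3.** Multiple imputation (20 imputations, Rubin's rules; 1,000 replicates) gave a proportion of 24.9–25.2%, with coverage of 94–96% for mean change and 95–98% for the proportion.

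**The case against.** The text does not use the word single, and it does not say that whole waves will be filled. EM might be meant only for skipped items. In a check with 10 items, n = 1,000 and 2–5% of items missing (all assumed), type I error was 4–7% and a true 25% read as 25.0%, so on that reading there is little harm. EM might also mean direct likelihood estimation inside the growth models, whose standard errors could then be valid. An article may leave the number of imputations to the full plan.

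It is true that single and whole-wave imputation are inferences. They remain the ordinary reading: the sentence speaks of imputing missing data without restriction, and no draws or pooling are named. Even if the growth models used direct likelihood, the cut-off proportions and prediction models would still need filled-in scores. The simulations test a mean change and a simple predictor effect, not the planned latent growth models, and type I error is not the relevant measure for the tree-based methods.

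A reader might infer four stronger points that the article does not support:

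- *The follow-up proportions will be too low.* Only if conditional means are used; with a random residual they are unbiased under MAR.
- *Imputation leaks validation data into the derivation set.* This rests on sentence order alone; the article fixes no sequence of operations.
- *Breastfeeding and similar items will be imputed for pregnant women.* The article says only "For postpartum women specifically, the survey also includes questions about" those topics; coding of non-applicable items is not stated.
- *All of the first objective is affected.* The comparison with pre-pandemic studies can use baseline data, which follow-up dropout does not touch.

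**Conclusion.** The point holds as a fault in a stated method, not as missing detail. On the ordinary reading, standard errors for follow-up change and risk-factor effects are too small with either kind of filled-in value. The error rate is about 10 to 14% in place of 5% at 20 to 30% missing and rises with dropout. Underestimation of the cut-off proportion is conditional on conditional-mean values. The direction follows from the method. The sizes rest on the assumed dropout, correlations, prevalence and MAR mechanism, and on missed waves being imputed. It should be corrected before the analysis.

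**What to change.** Replace the EM sentence in the Data analysis section with a statement of two methods.

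1. *Growth models:* fit by full-information maximum likelihood on the observed data, without imputation, with the predictors of dropout found in the attrition analysis as auxiliary variables. This gives that analysis a use.
2. *Cut-off proportions and prediction models:* use multiple imputation, imputing the score and then dichotomising it, pooled by Rubin's rules. Develop the imputation model in the 70% derivation data, then apply it to missing predictors in the 30% validation data.

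The cost is a change of wording, some additional analysis time and wider confidence intervals. Both methods still assume MAR, so they do not remove bias from dropout that depends on unobserved scores.

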### Participants

The study population consists of women during the perinatal period. The rationale is to evaluate women throughout their pregnancy and during 1 year after childbirth, for a six-month period (from baseline to follow-up). Women can, thus, enter the study during pregnancy or at any time during the first 6 months following childbirth [29].

The inclusion criteria at baseline are:
Being pregnant or a biological mother of a child six months of age or youngerWomen 18 years of age or olderLiving in one of the countries involved in the studyConsenting to participate in the study

The exclusion criteria are:
Not being currently pregnant or not being the biological mother of a child six months of age or youngerWomen younger than 18 years of ageLiving in a country that does not participate in the study.Not consenting to participate in the study

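### The stated scope of measurement equivalence is countries, but primary objective 1 rests on change over four waves during which many women pass from pregnancy to postpartum

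*Protocol article*

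**What the plan says.** The Data analysis section mentions measurement equivalence once: "Measurement equivalence will be studied in order to ensure we are measuring the same variables across countries". The following paragraph states how objective 1 will be analysed over time: "Changes in mental health between baseline and the follow-ups will be examined by testing latent growth curve models for each outcome". It also plans to relate rates of change in predictors to mental health results during follow-up.

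Under Aim, the first primary objective is "To evaluate changes in perinatal mental health outcomes (symptoms and indices of clinical risk for mental disorders) during the COVID-19 pandemic", and one stated part of it is "measuring the changes in perinatal mental health outcomes between the initial survey and the follow-up assessments". Comparison between participating countries is listed there among the secondary objectives.

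The Study design section sets four waves, "with a baseline and three follow-up assessments: at one, three, and six months post-baseline". On who is followed, the Participants section says: "Women can, thus, enter the study during pregnancy or at any time during the first 6 months following childbirth".

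The outcome sections define the EPDS, GAD-7 and PTSD levels as summed scores. The clinical cut-offs are 13 for the EPDS and 10 for the GAD-7, with no distinction between pregnancy and postpartum. Equivalence across waves, or between the two perinatal states, is not mentioned.

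**The concern.** A change in an observed score equals a change in the underlying symptom level only if the items relate to that level in the same way at each occasion. In this design, study time is tied to perinatal state: as the waves pass, more of the women who entered pregnant have delivered. Some items could plausibly be answered differently near term or with a newborn at the same level of distress. Examples are the PTSD items on concentration and on being watchful, and the somatic complaints that enter the BSI-18 total.

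If that happened, the shift would enter the growth slope of an outcome, or the rate of change of a predictor, and could be reported as an effect of the pandemic. The plan directs its equivalence check at the comparison between countries. That check also helps to justify pooling countries, but it says nothing about comparability over time.

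**Working it through.** The plan gives no figure on this point to reproduce. The check has three steps.

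**1. Which contrast is covered.**

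| Contrast | Role under Aim | Equivalence testing stated? |
|---|---|---|
| Between countries | Secondary objective | Yes |
| Baseline versus the three follow-ups | Primary objective 1 | No |
| Pregnant versus postpartum | Not an objective, but the state changes within women between waves | No |

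**2. How many women cross childbirth.** The article gives no gestational age at entry. Assume it is uniform from week *g* to week 40, with delivery at week 40. The share of women pregnant at baseline who have delivered after *w* weeks is then *w* / (40 − *g*), with *w* = 4.35, 13.04 and 26.09 for one, three and six months.

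| Earliest entry week *g* | 1 month | 3 months | 6 months |
|---|---|---|---|
| 0 | 10.9% | 32.6% | 65.2% |
| 4 | 12.1% | 36.2% | 72.5% |
| 8 | 13.6% | 40.7% | 81.5% |

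A majority has delivered only by the last wave. Without the uniform assumption, this requires more than half of the women pregnant at baseline to have entered at or beyond about 40 − 26.09 = 13.9 weeks. Women who enter postpartum do not make this transition.

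**3. What a shift would do, if there were one.** Take *g* = 4, no true change, and a shift of *b* points in the EPDS total at delivery. The apparent mean change in women pregnant at baseline is *b* × share delivered. For *b* = 1 it is 0.12, 0.36 and 0.72 points at the three follow-ups. Under these assumptions the pattern is a straight line in time (about 0.12 points per month), so a linear growth curve would fit these means and the fit indices would have no misfit in them to flag.

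For a simple baseline-to-six-month test, assume SD 5 and within-woman correlation 0.6. With *n* women pregnant at baseline, SE = √(2 × 25 × 0.4 / *n*), and the chance of a significant result is Φ(0.725*b* / SE − 1.96).

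| *n* | *b* | Apparent change | SE | Chance of rejection |
|---|---|---|---|---|
| 300 | 1.0 | 0.72 | 0.258 | 80% |
| 300 | 0.5 | 0.36 | 0.258 | 29% |
| 150 | 1.0 | 0.72 | 0.365 | 51% |
| 150 | 0.5 | 0.36 | 0.365 | 17% |

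A pooled version, with other assumptions, shows how far the answer depends on inputs. Two items shift by 0.3 each, 76% deliver by six months, and half the sample is pregnant at entry: 0.6 × 0.76 × 0.5 = 0.228 points, under 0.05 SD. With SD of change 5 × √0.8 = 4.47, the chance of rejection is 91% if all 14 × 300 = 4,200 women reach the last wave, about 65% with half retained, about 44% with 30% retained, and 14% with 300 women. These are two-wave tests, not the planned growth model, and none of the shift sizes comes from the documents.

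**The case against.** The strongest reply is that this is a condensed article. It does not say that equivalence will be tested across countries and nowhere else, and the occasions and levels of testing are detail that a full protocol or analysis plan may hold. That stands in part: a reader might infer that the sponsor has ruled out testing over time, and the text does not support this. But the article is not silent on equivalence. It states a purpose, and that purpose is attached to a secondary comparison while the contrast behind a primary objective is left out.

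A second reply is that the article does not say the growth models use sum scores. It refers to measurement equations, Lagrange multipliers and Wald tests, which could serve item-level models. That ambiguity is real. If the models use one score per wave, those tools cannot detect item shifts. If they use items, equality constraints over time are still needed, and none is stated.

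Third, the GAD-7 section cites good reliability and construct validity in pregnancy and postpartum. This is relevant, but it is not evidence of equal item functioning over time.

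A reader might also infer that the PTSD measure changes after baseline. The article says: "The subset of questions from the PTSD checklist are included in the COPE-IS and COPE-IU questionnaires". But the PTSD checklist section gives one list of ten items, one recall period and one response scale, and Table 1 places these items in the COPE-IS and COPE-IU only, not in the COPE-CF. The caveat that "COPE-IS, COPE-IU and COPE-CF are newly developed measures, and psychometric properties are yet to be established" concerns the COPE measures. For the repeated COPE sections the article gives one item list each, so no difference between baseline and follow-up forms is shown, and there is no ground for excluding COPE predictors from the change analysis.

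**Conclusion.** The concern holds as a mismatch of scope: the stated equivalence testing does not cover the contrast on which the longitudinal part of primary objective 1 depends. The consequence is a possible bias. A reader might go further and conclude that the growth slopes will show a false pandemic effect, or that most women pregnant at entry change state throughout follow-up. The documents support neither. They report no item shift, and a majority delivers only by six months, under an assumed entry distribution. The illustrated sizes range from negligible to detectable, and they depend on the assumed shift, SD, correlation and retention; follow-up is optional and no retention rate is given.

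The point also does not touch the comparison with pre-pandemic studies or the proportions above the cut-offs as such, which longitudinal equivalence would not settle. It should be acted on because the data to test the assumption are already being collected. Confidence is medium, since a fuller plan may address it.

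**What to change.** Extend the planned equivalence testing to (a) the four waves and (b) pregnant versus postpartum women. Apply it to the EPDS, the GAD-7, the ten PTSD items and any multi-item predictor whose rate of change is analysed, for example the BSI-18.

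State in advance what follows if scalar (intercept) equivalence fails: report a partial-invariance latent growth model beside the sum-score model as a sensitivity analysis, and qualify conclusions about change where the two differ. Keep the sum scores for the cut-offs of 13 and 10 and for comparison with pre-pandemic studies, because a latent factor with freed items is no longer on that metric. The article should also say whether the growth models are fitted to total scores or to items.

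The cost is additional models on data already collected, with structural equation software already planned, and possibly more cautious conclusions about change.
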